#### Secondary objectives

To prospectively correlate different MRI sequences and FDG-PET findings with disease-free survival (DFS) and overall survival (OS)To determine the best time to perform MRI during radiotherapy treatment for assessing tumour response and local controlTo determine the sensitivity and specificity of functional MRI sequences compared with FDG-PET in assessment of potential residual and recurrent MPHNC following definitive radiotherapyTo assess consistency of image registration, signal information and associated analyses over a relevant time frame in a representative subset of patients

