### Statistical plan

#### Sample size determination

Based on our previous study using week 3 FDG-PET scan in head and neck cancer patients, the following sample size calculation is made. To test a significant FDG-PET complete metabolic response (CMR) rate of 87% in the MRI-positive group versus an FDG-PET CMR rate of 51% in the MRI-negative group, the study will need to recruit 55 patients in total to reach 80% power (at 5% significance level). This number is based on an assumption that the MRI-positive group and MRI-negative group will be balanced (e.g. 50%:50% but is powered to allow up to a 40%:60% biased ratio). It is anticipated that recruitment will be completed in 24 months. Patients will be offered participation in the “hop on hop off” sub-study, with a recruitment goal of 20.

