#### Assessment of MRI sequences

MRI scans will be determined as a good response (e.g. positive) or poor response (e.g. negative) based on the following definitions for endpoint analysis:

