##### DWI

High ADC values will be considered a good response (positive MRI) and low ADC values a poor response (negative MRI).

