#### Statistical analysis

Statistical analyses will be performed by using software SPSS and *p* < 0.05 will be considered statistically significant. Chi-square test will be used to compare the prevalence of FDG-PET CMR between MRI-positive and negative groups. Comparisons of the ADC values/maps of pre-, intra- and post-treatment DWI images will be performed by using one way analysis of variance (ANOVA) test. Comparisons of the DCE parameters such as K^trans^, K_ep_, area under the curve (AUC) at initial 60 and 90 s of pre-, intra- and post-treatment will be performed by using the Kruskal-Wallis test. To determine the sensitivity and specificity of DWI and DCE parameters for FDG-PET CMR and 12 month local control, Kappa association statistics will be used. Receiver operator characteristics (ROC) will be used to obtain an optimal threshold for individual MRI parameters.

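### Kappa is named as the method for sensitivity and specificity but estimates neither, and the target condition differs between the objectives and the analysis section

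*Protocol article*

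**What the plan says.** The protocol article's Statistical analysis section assigns a method to the accuracy question: for the sensitivity and "specificity of DWI and DCE parameters for FDG-PET CMR and 12 month local control, Kappa association statistics will be used". The next sentence gives ROC analysis a different job: "Receiver operator characteristics (ROC) will be used to obtain an optimal threshold for individual MRI parameters".

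The coding of the MRI result is set under Assessment of MRI sequences: "MRI scans will be determined as a good response (e.g. positive) or poor response (e.g. negative". The DWI, DCE MRI and BOLD definitions that follow keep to it; for DWI, high ADC is positive and low ADC is negative.

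The accuracy aim is set under Secondary objectives as the "sensitivity and specificity of functional MRI sequences compared with FDG-PET in assessment of potential residual and recurrent MPHNC" after definitive radiotherapy. The Secondary endpoints likewise ask whether DWI can pick up disease that persists or returns. Neither place says which MRI result counts as test-positive for that purpose.

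**The concern.** Two things do not fit.

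First, the method does not match the quantity. Sensitivity and specificity are two conditional proportions. Kappa compresses the 2x2 table into one number that also depends on the margins. An analyst who follows the sentence literally would report a kappa and leave the stated objective unanswered.

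Second, the target condition is not aligned. With CMR or local control as the condition and good response as the positive result, sensitivity is the probability of a good-response MRI among patients with CMR. For residual disease that same proportion is the specificity, and the plan's specificity becomes the sensitivity. If the figures were reported under the analysis section's labels as an answer to the residual-disease objective, the reader would take the wrong one as the chance of detecting residual disease. Kappa would not reveal this, because it is unchanged when both labels are reversed.

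**Working it through.** **Inputs** (Sample size determination): CMR rate 87% if MRI-positive and 51% if MRI-negative; 55 patients; 80% power; 5% level; split "50%:50% but is powered to allow up to a 40%:60% biased ratio". Sidedness is not stated, so two-sided is assumed. The text does not say which group is the larger, so both directions are shown.

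**The plan's own figure.** The usual two-proportion formula without continuity correction gives 25 + 25 = 50 patients at 50:50 and 21 + 32 = 53 at 40:60 (MRI-positive:negative). At 55 patients the approximate power is 0.84 and 0.82. The stated 55 is reproduced to within 2 of the 40:60 figure. It rests on the chi-square comparison, not on kappa.

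**The 2x2 table implied at 50:50** (proportions of all patients):

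| | CMR | no CMR |
|---|---|---|
| MRI-positive | 0.5 × 0.87 = 0.435 | 0.5 × 0.13 = 0.065 |
| MRI-negative | 0.5 × 0.51 = 0.255 | 0.5 × 0.49 = 0.245 |

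- CMR prevalence = 0.435 + 0.255 = 0.69
- P(MRI+ | CMR) = 0.435 / 0.69 = 0.63
- P(MRI− | no CMR) = 0.245 / 0.31 = 0.79
- Observed agreement = 0.435 + 0.245 = 0.68
- Chance agreement = 0.5 × 0.69 + 0.5 × 0.31 = 0.50
- Kappa = (0.68 − 0.50) / (1 − 0.50) = 0.36

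**Kappa does not identify the pair.** At the same prevalence of 0.69, a kappa of about 0.36 also arises from sensitivity/specificity of 0.75/0.63, 0.85/0.49 and 0.90/0.43. For 0.75/0.63:

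- Agreement = 0.75 × 0.69 + 0.63 × 0.31 = 0.713
- P(MRI+) = 0.75 × 0.69 + 0.37 × 0.31 = 0.632
- Chance agreement = 0.632 × 0.69 + 0.368 × 0.31 = 0.550
- Kappa = (0.713 − 0.550) / 0.450 = 0.36

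**Kappa moves with prevalence.** Hold 0.63/0.79 fixed (unrounded values used) and vary the CMR prevalence over the range that the plan's rates and splits imply. That range runs from 0.4 × 0.87 + 0.6 × 0.51 = 0.654 to 0.6 × 0.87 + 0.4 × 0.51 = 0.726.

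- At 0.654: agreement 0.686, chance 0.495, kappa = 0.190 / 0.505 = 0.38
- At 0.726: agreement 0.674, chance 0.507, kappa = 0.167 / 0.493 = 0.34

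The shift within this range is modest.

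**The label reversal over the allowed splits** (87% and 51% fixed):

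| MRI+ : MRI− | Target CMR: sens / spec | Target residual disease: sens / spec | Gap | Kappa |
|---|---|---|---|---|
| 40:60 | 0.532 / 0.850 | 0.850 / 0.532 | 31.8 points | 0.33 |
| 50:50 | 0.630 / 0.790 | 0.790 / 0.630 | 16.0 points | 0.36 |
| 60:40 | 0.719 / 0.715 | 0.715 / 0.719 | 0.4 points | 0.38 |

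Kappa is the same for both targets in every row.

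**The case against.** The best defence is that the protocol names sensitivity and specificity as what is wanted, and that the planned ROC analysis is built from exactly those proportions at every cut-point. The objective is therefore within reach of the planned data and software. That stands, and it rules out the stronger claim that the objective cannot be answered. It does not repair the sentence, because ROC is given only the threshold role and kappa is the method named for accuracy. Nor is this a detail left to a fuller document: the article states a method, and the method is the wrong one.

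A reader might also infer that the plan wrongly swaps sensitivity and specificity. The documents do not support that. The analysis section names CMR and local control as its targets, both favourable outcomes, and pairing them with a favourable MRI result as positive is coherent. The reversal appears only when those figures are carried over to the residual-disease objective. It then relabels two numbers from the same table and loses no data.

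The size of the point can be overstated too. The 87% and 51% are sample-size inputs taken from earlier week 3 FDG-PET work, not accuracy assumptions for post-treatment DWI or DCE. The 16-point gap belongs to the 50:50 split alone. Letting CMR prevalence run from 50% to 90% would move kappa from 0.42 to 0.18, but that goes well beyond the roughly 65% to 73% that the plan implies.

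**Conclusion.** The point holds in two parts. Kappa is the wrong method for the stated quantities: on the planning rates a single value of about 0.36 is compatible with pairs from 0.63/0.79 to 0.90/0.43. And the target condition is not aligned between the Secondary objectives and endpoints (residual or recurrent disease) and the coding and analysis sections (CMR and local control, good response positive). Carrying the labels across would misstate each figure by about 0 to 32 points over the allowed splits, and by 16 points at 50:50.

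These sizes assume the planning CMR rates and a single binary MRI result. They illustrate the problem and do not predict the trial's accuracy. The document gives no planning rate for 12-month local control, so no size is given for that target.

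This should be fixed, but it does not threaten the trial. The objective is secondary, and data collection, the chi-square comparison and the sample size of 55 are unaffected.

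**What to change.** Replace the kappa sentence with one stating that sensitivity and specificity will be estimated directly from the 2x2 table of MRI result against each reference outcome, with exact or Wilson 95% intervals. The intervals matter here: the planning rates imply only about 55 × 0.31 = 17 patients without CMR, whichever statistic is named.

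Add a second sentence giving, for each accuracy analysis, the target condition and the MRI result that counts as test-positive. For the residual-disease objective, poor response should be the positive result and absence of CMR, or local failure, the condition. The present coding can stay for analyses that target CMR or local control. Kappa may be kept as a descriptive measure of agreement between MRI and PET, labelled as such.

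The cost is two sentences of text. No extra patients, scans or data are needed.

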Our group completed a pilot study of functional MRI and FDG-PET in a cohort of patients undergoing radical radiotherapy for MPHNC, indicating that carrying out sequential DWI and R2* studies before, during and after radiotherapy was feasible. Initial results, including correlations between imaging studies have been published, while mature data regarding clinical outcomes are awaited [18]. Following this we have initiated a prospective observational study named “MRI in MPHNC”, which aims to gather data on the utility of functional imaging sequences with DWI, DCE and BOLD MRI as biomarkers for prediction and assessment of treatment response.

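### The ADC cut-off is not fixed, and the only stated way to set one is an outcome-driven ROC optimum; if that forms the tested groups, the false-positive rate is about 7–20%, not 5%

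*Protocol article*

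**What the plan says.** Under Assessment of MRI sequences, scans are classed as positive or negative for the endpoint analysis. The DWI rule is: "High ADC values will be considered a good response (positive MRI) and low ADC values a poor response (negative MRI"). It gives a direction but no number. The DCE and BOLD rules differ in kind: a fall in the parameter is positive, and no change or a rise is negative. Their cut-off is therefore zero change.

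Statistical analysis then says: "Chi-square test will be used to compare the prevalence of FDG-PET CMR between MRI-positive and negative groups", with significance at p < 0.05. The same section seeks sensitivity and specificity of DWI and DCE parameters for metabolic response and 12-month local control, and ends: "Receiver operator characteristics (ROC) will be used to obtain an optimal threshold for individual MRI parameters". It does not name the ROC criterion, the sample in which the threshold is found, or the analyses that will use it.

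Sample size determination rests on the comparison of MRI groups: "To test a significant FDG-PET complete metabolic response (CMR) rate of 87% in the MRI-positive group". The rate assumed for MRI-negative patients is 51%. On that basis, "the study will need to recruit 55 patients in total to reach 80% power (at 5% significance level"). It assumes balanced groups and allows for a split of up to 40:60.

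**The concern.** High and low ADC groups cannot be formed without a cut-off, and the only cut-off method in the article is one that uses the outcome. Such a cut-off is the one, among all those available, at which the groups differ most (or nearly most) on the outcome. A chi-square test that treats it as given in advance ignores that search, so its p-value is too small. The 5% level, and the 80% power tied to it, would then not describe the test that is run.

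Sensitivity and specificity quoted at a cut-off tuned on the same patients are too favourable as well, whether or not a chi-square test follows. The Discussion says the results will help define which sequences and time points can be used to adapt radiotherapy and will feed into interventional studies. An over-optimistic ADC cut-off would pass into those designs.

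**Working it through.** **Inputs from the protocol article.** N = 55; response rates 87% and 51%; 80% power; 5% level; split 50:50, up to 40:60; direction fixed (high ADC is good).

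**Assumed, because not stated.** Two-sided test; overall response rate (0.87 + 0.51)/2 = 69%, about 38 of 55; all 55 patients evaluable; one ADC measure at one time point; ROC criterion and continuity correction varied below.

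**1. The plan's own figure.** With pooled variance, no continuity correction and k = n2/n1:

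n1 = [1.96·√(p̄(1−p̄)(1+1/k)) + 0.8416·√(p1q1 + p2q2/k)]² / (p1−p2)²

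- 50:50: p̄ = 0.69. [1.96·√0.4278 + 0.8416·√0.3630]² / 0.1296 = (1.282 + 0.507)² / 0.1296 = 24.7, so 25 per group and 50 in total.
- 40:60 with the 87% group smaller (k = 1.5): p̄ = 0.654. [1.96·√0.3771 + 0.8416·√0.2797]² / 0.1296 = (1.204 + 0.445)² / 0.1296 = 21.0, so 21 + 32 = 53.

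The stated 55 is reproduced to within two patients. Power at 55 is 84.3% (50:50) and 82.0% (22:33). The sample size is sound for groups formed without sight of the outcome.

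**2. Why the search matters.** Let J = sensitivity + specificity − 1. For a cut that leaves nH patients high and nL low, with 38 responders and 17 non-responders, the Pearson statistic is

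X² = N·38·17·J² / (nH·nL) = 35,530·J² / (nH·nL).

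At 27:28, X² passes 3.84 when J > √(3.84·756/35,530) = 0.286. At 10:45 it passes when J > √(3.84·450/35,530) = 0.221. There are 54 possible cuts in 55 ordered values. Youden's rule takes the largest J among them, and uneven splits need a smaller J to reach significance.

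**3. False-positive rate with a marker unrelated to response.** 40,000 simulated trials, 55 patients, response rate 69%, direction fixed, threshold 3.84:

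| How the cut-off is set | Pearson | Yates-corrected |
|---|---|---|
| Median, without the outcome | 4.7% | 2.4% |
| Youden, any split | 19.7% | 9.3% |
| Youden, at least 10% in each group | 17.6% | 8.8% |
| Youden, at least 25% in each group | 12.9% | 6.8% |
| Youden, split within 40:60 | 7.8% | 4.0% |
| Closest to top-left corner, any split | 10.7% | 5.6% |
| Closest to top-left corner, within 40:60 | 7.5% | 3.7% |

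The Monte Carlo standard error is at most 0.25 points. With exactly 38 responders in every trial, the figures are 20.3% (Youden, any split), 9.8% (top-left), 6.9% (Youden within 40:60) and about 4.3% (median). Over response rates of 51–87%, unrestricted Youden stays at 19.7–20.2% and the median split at 4.7–5.8%.

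**4. Apparent accuracy.** In the same null setting with 38 responders, the mean J at the Youden cut-off is 0.165, when the true value is 0.

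**The case against.** The strongest reply is that no sentence says the ROC threshold defines the chi-square groups. The groups are defined under Assessment of MRI sequences, and the ROC sentence comes last, after the one on sensitivity and specificity, so it may serve only that description. This stands: the link is an inference. It does not remove the point for ADC, because no other source of a cut-off is given and the grouping cannot be made without one. The bias in sensitivity and specificity does not depend on the link.

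A reader might go further in three ways that the article does not support.

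- *That every MRI comparison is affected.* The DCE and BOLD groups have a zero-change rule. ROC would reach their chi-square tests only by overriding that rule, which the article does not say.
- *That the error is about seven times nominal.* The corresponding 36.0% requires the direction to be chosen from the data as well. The article fixes direction for all three sequences.
- *That counting sequences and scans makes a false positive nearly certain.* That is mostly multiplicity. Three sequences at six on- and post-treatment scans make 18 tests, and 18 independent valid 5% tests already give 1 − 0.95^18 = 60% with no cut-point search.

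It is also fair that a condensed article may leave the ROC criterion and any optimism correction to a fuller document, and that this is an observational study that changes no treatment. The point rests on the threshold method the article does state, not on missing detail.

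**Conclusion.** The concern holds for ADC, conditionally. The article fixes direction but no cut-off, and the one method it offers uses the outcome. If that method forms the tested groups in the same 55 patients, the uncorrected Pearson test has a false-positive rate of about 20% under Youden with unrestricted search, roughly four times nominal. The range is roughly 7–20% across the ROC criteria and splits tried at a 69% response rate. A Yates correction lowers these figures, in some settings to below 5%, so no single multiple can be quoted as fact. Accuracy at an ROC-chosen cut-off in the same patients is biased upward in any case, by about 0.17 on the Youden index when there is no association. The sample size calculation is not in error.

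**What to change.** 1. For the tested ADC comparison, set the cut-off without using this trial's outcomes. The cohort median does this and also gives the balanced split assumed in the sample size. Alternatively, test ADC as a continuous variable, by logistic regression for complete metabolic response and AUC with a 95% confidence interval.
2. State that the zero-change rule, not ROC, governs the DCE and BOLD chi-square groups.
3. Label ROC-derived cut-offs exploratory, attach no chi-square p-value to them, and report their sensitivity and specificity with bootstrap or cross-validated optimism correction.

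The pilot is a less certain source of a cut-off. The Background says it showed that "carrying out sequential DWI and R2* studies before, during and after radiotherapy was feasible", but also that its mature clinical outcomes are still to come, so the article does not show that it can yet supply an outcome-based threshold.

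The cost is a change of wording and a little more analysis work, with no extra patients or scans. The price is slightly less favourable apparent accuracy.

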### Data collection

General baseline demographic data will be collected. Other data collection can be defined by the 6 general categories below:

#### Quality of life

BaselineFinal week of chemoradiotherapyFollow up visits 1, 3, 6, 12, 18, 24, 30 and 36 months post treatmentAssessed using University of Washington Quality of Life Questionnaire (UW-QOL v4)[40]

#### Blood tests

BaselineWeeks 2, 3, 5, 6Follow up visits 1 and 3 months post-treatmentConsist of full blood count and basic biochemistry panel including urea, creatinine, sodium, potassium and chloride

#### Toxicity

Acute toxicities – dry mouth, dysphagia, pain, weight loss, oral mucositis, radiation dermatitis, dygeusia,Baseline, weekly during treatmentFollow up visits 1 and 3 months post treatments
Late toxicities – dry mouth, skin induration, osteonecrosis of jaw, voice alteration, oral mucositis, dysphagia, hearing, tracheostomy, laryngectomy, tube feedingAt follow up visits 3, 6, 12, 18, 24, 30 and 36 months post treatment
Using CTCAE version 4.0Serious adverse events to be reported to the HREC for review

#### Swallowing assessment

BaselineFinal week of chemoradiotherapyFollow up visits 1, 3, 6, 12, 18, 24, 30 and 36 months post treatment

#### Scans

Functional MRI scans as per Fig. 1 and *Imaging procedures* aboveAs per standard of care, a PET/CT will be carried out at week 3 of chemoradiotherapy treatment and then at 3 months following completion of chemoradiotherapy treatment

#### Treatment data

The dose and duration of treatment will be recorded.

### Data handling and record keeping

All imaging datasets will be de-identified and stored in a secure research drive at the Cancer Therapy Centre, Liverpool Hospital after recruiting patients to the study. Contours will be performed by radiation oncologists/fellows and saved on the research drive. Datasets will be imported into MATLAB (MathWorks Inc. Massachusetts, United States) and similar mathematical analysis programs for data-analysis. Data analysis will be in line with study aims.

The investigator site file and patient study file will be kept at the Ingham Institute Liverpool and will be accessible only by clinical trials staff.

#### Confidentiality

Subject confidentiality is strictly held in trust by the participating investigators, research staff, the sponsoring institution and their agents. The study documentation, data and all other information generated will be held in strict confidence. No information concerning the study or the data will be released to any unauthorized third party, without prior written approval of the HREC and the principal investigator. Clinical information will not be released without written permission of the subject, except as necessary for monitoring by Human Research Ethics Committee (HREC) or regulatory agencies.

#### Records retention

It is the investigators’ responsibility to retain study essential documents for at least 15 years after the completion of this clinical trial. All information will be stored in the Radiation Oncology research office located at the Ingham Institute, Liverpool Hospital, either on a password protected computer or in files kept in a locked room. Access to this information will be limited to the principal investigator, research assistants and statistician as authorized by the delegation log.

### Timelines/milestones

The study started recruitment after ethics approval was granted. A sample size of 55 has been selected for this study for the reasons discussed above. Initial projections suggested this could be achieved within 24 months, however this timeframe will be reviewed as recruitment progresses.

### Publication and dissemination

The results of the study will be submitted for publication in peer-reviewed journals and for presentation at scientific meetings. Participants in the study will be notified of study results in writing.

## Discussion

In recent years intensity-modulated RT, along with advanced diagnostic and on-treatment imaging technologies, have improved the therapeutic ratio in head and neck cancer [41]. The enhanced ability to dose-paint and the recognition of heterogeneity within tumours gives rise to the promise of functional image-guided RT (fIGRT), where subvolumes may be treated to differing doses according to imaging-derived parameters. Longitudinal diffusion-weighted imaging has already been shown to be feasible in MRI-guided cobalt radiotherapy systems [42], suggesting that the addition of functional as well as anatomical imaging may serve to improve outcomes with these systems, as well as in the MRI-guided linear accelerators in development.

Our protocol builds on our earlier work which established the feasibility of serial functional MRI during a course of treatment for MPHNC. Refinements to the imaging protocol include the addition of DCE sequences, which may be expected to add further value [43], and the expansion of the BOLD sequence to acquire multiple slices across a volume, an imaging technique which may be more reliable than BOLD imaging carried out on single slices [44]. The additional information gained from the enhanced suite of imaging sequences in the current study will help to define which sequences, at which time points, can be used to adapt and personalise radiotherapy treatment. This information will then feed into the design of interventional studies of adaptive RT.

